## Abstract

**Background:**

Glioblastoma (GBM) is the most aggressive type of brain cancer, with a 5-year survival rate of ~5% and most tumours recurring locally within months of first-line treatment. Hypoxia is associated with worse clinical outcomes in GBM, as it leads to localized resistance to radiotherapy and subsequent tumour recurrence. Current standard of care treatment does not account for tumour hypoxia, due to the challenges of mapping tumour hypoxia in routine clinical practice. In this clinical study, we aim to investigate the role of oxygen enhanced (OE) and blood-oxygen level dependent (BOLD) MRI as non-invasive imaging biomarkers of hypoxia in GBM, and to evaluate their potential role in dose-painting radiotherapy planning and treatment response assessment.

**Methods:**

The primary endpoint is to evaluate the quantitative and spatial correlation between OE and BOLD MRI measurements and [^18^F]MISO values of uptake in the tumour. The secondary endpoints are to evaluate the repeatability of MRI biomarkers of hypoxia in a test-retest study, to estimate the potential clinical benefits of using MRI biomarkers of hypoxia to guide dose-painting radiotherapy, and to evaluate the ability of MRI biomarkers of hypoxia to assess treatment response. Twenty newly diagnosed GBM patients will be enrolled in this study. Patients will undergo standard of care treatment while receiving additional OE/BOLD MRI and [^18^F]MISO PET scans at several timepoints during treatment. The ability of OE/BOLD MRI to map hypoxic tumour regions will be evaluated by assessing spatial and quantitative correlations with areas of hypoxic tumour identified via [^18^F]MISO PET imaging.

**Discussion:**

MANGO (Magnetic resonance imaging of hypoxia for radiation treatment guidance in glioblastoma multiforme) is a diagnostic/prognostic study investigating the role of imaging biomarkers of hypoxia in GBM management. The study will generate a large amount of longitudinal multimodal MRI and PET imaging data that could be used to unveil dynamic changes in tumour physiology that currently limit treatment efficacy, thereby providing a means to develop more effective and personalised treatments.

## Introduction

1

Glioblastoma (GBM) is the most aggressive type of brain cancer and carries an extremely poor prognosis, which is reflected in 5-year survival of 5% and an overall median survival time of approximately 17 months following first-line treatment (1). After standard of care treatment, involving maximal safe resection of the bulk tumour mass followed by adjuvant chemoradiation treatment, most tumours recur locally, highlighting the failure of current treatment approaches to sustain local control (2, 3). The large intra- and inter-tumour heterogeneity characterising GBMs and the ability of GBM cells to dynamically adapt during the course of treatment and develop treatment resistance mechanisms are causes of local treatment failure (4). As such, the future of improved treatment outcomes for GBM patients relies on personalised treatment strategies targeting known mechanisms of treatment resistance.

Hypoxia, which is often present in subregions of GBM tumours, is the leading cause of resistance to radiotherapy, is predictive of the local sites of recurrence and is associated with poor clinical outcomes in GBM (5–12). Current standard of care treatment does not account for tumour hypoxia. The ability to image tumour hypoxia at various stages of treatment offers opportunities to personalise and improve treatments for GBM patients (13). For instance, preoperative imaging of tumour hypoxia offers the opportunity for supramarginal resections in surgical planning beyond current neurosurgical standard of care guidelines (14). Identifying hypoxic regions by using specialised imaging potentially allows adaptive radiotherapy treatment planning and delivery strategies to selectively dose escalate to radioresistant tumour regions, thus increasing the likelihood of local control (10, 15). Identifying hypoxic tumour regions harbouring progression at follow up is key to intervening at an early stage of tumour recurrence and personalising therapy tailored to the tumour response to treatment (16).

Imaging of tumour hypoxia in routine clinical practice is challenging, as it requires [^18^F]MISO PET (13, 17), which is not available in most clinical centres (18). MRI, which is the core imaging modality in the management of GBM patients and is available at most clinical sites, offers a more cost effective and accessible means to integrating imaging biomarkers of hypoxia into clinical workflows (19, 20). Additionally, the combination of MRI screening with radiotherapy is becoming more common with the growth in integrated MRI-guided radiotherapy systems (21). In this clinical imaging study, we aim to validate oxygen enhanced (OE) and blood-oxygen level dependent (BOLD) MRI as imaging biomarkers of hypoxia at different stages of GBM treatment, and evaluate potential patients benefits arising from their integration into radiotherapy treatment planning and in treatment response assessment.

Several preclinical studies have already shown the ability of OE/BOLD MRI to identify areas of hypoxic tumour and use this information to improve cancer treatment and response assessment. For instance, Zhou et al. demonstrated that OE/BOLD MRI measurements correlate with levels of [^18^F]MISO uptake in hypoxic tumour of a rat prostate cancer model (22), thus showing its potential as an alternative, non-invasive imaging biomarker of hypoxia. White et al. have shown the ability of OE MRI to predict tumour response to radiation treatment in a preclinical model of prostate cancer, thus showing the potential of OE MRI for adaptive radiotherapy treatment strategies (23). This finding was further confirmed by Arai et al., who demonstrated the predictive value of OE MRI in response to radiation treatment in a rat model of prostate cancer (24). The authors additionally showed an improvement in tumour control resulting from the delivery of a 10 Gy boost of radiation dose to hypoxic tumours identified with OE MRI (24). Beeman et al. have demonstrated that OE MRI has the ability to differentiate progressing tumour lesions from radiation necrosis lesions in a preclinical glioma study (25), showing OE MRI potential for improved response assessment applications. Finally, in a recent clinical study Lickliter et al. demonstrated the utility of OE MRI to assess tumour response to the administration of a novel hypoxia modifying agent in combination with standard chemoradiation therapy in GBM patients (26).

Overall, by performing this study, we expect to provide a non-invasive, more effective means to adapt treatment to the individual tumour characteristics of each patient, that can be accessible to many clinical centres worldwide.

## Methods and analysis

2

### Study objectives

2.1

The study has one primary and four secondary objectives (**Figure 1**). The primary objective is to evaluate the spatial and quantitative correlations between OE and BOLD MRI measurements of hypoxia and [^18^F]MISO values of uptake in the tumour once before patients receive surgery and once prior to commencement of chemoradiation treatment. The secondary objectives are: 1) to evaluate the repeatability of the MRI biomarkers of hypoxia by means of test-retest scans acquired prior to patients commencement of chemoradiation treatment; 2) to develop a framework to integrate image-derived tumour hypoxia information into radiation treatment plans and estimate the potential clinical benefits of this approach compared to conventional radiation treatment; 3) to evaluate the ability of MRI biomarkers of hypoxia to assess tumour response to chemoradiation treatment; 4) to evaluate whether changes in the MRI biomarker of hypoxia observed during chemoradiation treatment are predictive of patient overall survival. Secondary objectives 3 and 4 of this study are exploratory.

**Figure 1 f1:**
[figure not shown]
Diagram of study objectives and study interventions timeline.

### Study hypotheses

2.2

**
*Primary objective:*
** MRI measurements of tumour hypoxia levels directly correlate to measurements of [^18^F]MISO PET uptake.

**
*Secondary objective 1:*
** MRI measurements of hypoxia in the tumour volume acquired in the test-retest scans have excellent repeatability.

**
*Secondary objective 2*
**: Dose-painting radiotherapy plans that target areas of hypoxic tumour with high doses of radiation will result in improved modelled local tumour control probability and minimal alteration to normal tissue dose tolerances compared to standard radiotherapy plans.

**
*Secondary objective 3*
**: MRI measurements of tumour hypoxia at 12 weeks post chemoradiation treatment completion spatially overlap with sites of local recurrence and negatively correlate with patient overall survival time.

**
*Secondary objective 4*
**: Increases in measurements of tumour hypoxia observed during chemoradiation treatment negatively correlate with patient overall survival time.

### Study outcome measures

2.3

#### Primary objective

2.3.1

Spatial correlation between hypoxic tumour volume (HTV) determined with MRI and [^18^F]MISO will be evaluated via measurements of Dice similarity coefficient. Dice similarity coefficients > 0.75 will be considered a good spatial correlation. Quantitative correlation of voxel-wise and HTV-average levels of hypoxia will be evaluated via measurement of the Pearson’s correlation coefficient. Correlation coefficients > 0.7 will be considered a strong correlation (27).

#### Secondary objective 1

2.3.2

Repeatability of voxel-wise and HTV-average levels of hypoxia in the tumour, calculated as explained below for each hypoxia imaging biomarker, will be assessed via measurements of intraclass correlation coefficient (ICC). Repeatability is considered excellent, good, moderate or poor for ICC values > 0.9, 0.75-0.9, 0.5- 0.75 and< 0.5, respectively. Additionally, similarity between the HTV defined with the MRI biomarker at the two timepoints will be assessed via calculation of Dice similarity coefficient. Dice similarity coefficients > 0.9 will be considered a strong correlation.

#### Secondary objective 2

2.3.3

The predicted patient benefits of the hypoxia-guided dose-painting radiotherapy plan will be compared with the actual patient outcomes following conventional treatment, by using metrics including modelled tumour control probability (TCP) and toxicity measurement to organs at risks and healthy brain (including equivalent uniform dose). Voxel-wise dose-painting prescriptions within the conventional radiotherapy targets will be escalated from 60 Gy based on the level of hypoxia determined by the selected MRI imaging biomarker according to the method previously described by Toma-Dasu et al. (28). Targets delineation and constraints to organs at risk as per ESTRO-EANO guidelines (29) will be set equally for the optimisation of the conventional and dose-painting plans. Success for this objective will be achieved if the dose-painting plans result in improved TCP by more than 15% over conventional treatment, while dose metrics to organs at risk remain similar.

#### Secondary objective 3

2.3.4

Spatial correlation between HTV after completion of chemoradiation treatment and volume of recurrent tumour at relapse evaluated with standard anatomical imaging will be evaluated via measurements of Dice similarity coefficient. Dice similarity coefficients > 0.9 will be considered a strong spatial correlation. Correlation between the percentage of HTV after completion of chemoradiation treatment and clinical outcome will be evaluated by means of hazard ratio obtained from Cox regression. A hazard ratio > 1 (p<0.05) will indicate that the HTV at suspected recurrence is associated with worse patient overall survival.

#### Secondary objective 4

2.3.5

Correlation between the percentage change of HTV during treatment and patient clinical outcome will be evaluated by means of hazard ratio obtained from Cox regression. A hazard ratio > 1 (p<0.05) will indicate that the increase in HTV during treatment is associated with worse patient overall survival. Given the known prognostic role of sex and age on GBM overall survival (30–32), sub-analyses assessing whether HTV increase during treatment has a sex/age-specific impact on overall survival will be performed.

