### Statistical analysis

2.10

The sample size required for this study was calculated from a power analysis performed with the software GPower v.3.1. based on the hypothesis linked to the primary objective of the study. The hypothesis is that OE and BOLD MRI measurements of hypoxia within the tumour lesion will positively correlate (Pearson correlation coefficient > 0.7) to [^18^F]MISO values of uptake. The statistical test used in the power analysis was a correlation test using a point biserial model. Based on a Pearson correlation coefficient of 0.7, which was previously reported for the correlation of MRI measurements of hypoxia and the gold-standard immunohistochemical marker of hypoxia pimonidazole (27), the minimum sample size required to answer the hypothesis with 98% power and 5% two-tailed alpha, is 19. As such, up to 20 patients will be recruited for this study. A sample size of N=20 patients, which is large compared to the usual sample size used to estimate repeatability of ROI-averaged quantitative imaging measures (46), will allow us to test the hypothesis linked to secondary objective 1 - involving assessing the repeatability of OE/BOLD MRI measurements of hypoxia with the test-retest scan - with a specificity of at least 85% with 95% certainty (47); and the hypothesis linked to secondary objective 2 – involving the assessment of whether dose-painting radiotherapy plans result in improved TCP by more than 15% over conventional treatment - with 99% power and 5% one-tailed alpha (calculated with GPower v.3.1.).

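### Secondary objective 2 names two conflicting comparators, and if one MRI map both paints the dose and scores TCP, its >15% rule can be met without locating hypoxia

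*Protocol article*

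**What the plan says.** Section 2.3.3 opens by stating that the predicted benefit of the hypoxia-guided plan "will be compared with the actual patient outcomes following conventional treatment", and names the yardsticks: "by using metrics including modelled tumour control probability (TCP) and toxicity measurement to organs at risks and healthy brain". The rest of the section describes a plan-against-plan exercise. Targets and organ-at-risk constraints "will be set equally for the optimisation of the conventional and dose-painting plans", and the rule is: "Success for this objective will be achieved if the dose-painting plans result in improved TCP by more than 15% over conventional treatment", with organ-at-risk dose metrics also staying similar. Section 2.2 likewise words the hypothesis plan against plan: "improved modelled local tumour control probability and minimal alteration to normal tissue dose tolerances compared to standard radiotherapy plans".

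The prescription is "escalated from 60 Gy based on the level of hypoxia determined by the selected MRI imaging biomarker". No section names the hypoxia map that enters the TCP calculation. Section 2.4 treats [18F]MISO PET as the reference for hypoxia but does not tie it to this objective. Section 2.10 states that 20 patients allow this hypothesis to be tested "with 99% power and 5% one-tailed alpha", and gives no SD, baseline TCP or assumed gain.

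**The concern.** Three things are at stake.

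- **Comparator.** A modelled probability for one plan and an observed outcome under the other are different quantities. Their difference mixes the effect of the plan with the error of the model.
- **Scoring map.** Dose goes up where MRI calls the tumour hypoxic. If TCP is then computed with the same MRI map as the truth, the painted plan is rewarded for agreeing with itself. The gain would carry no information on whether MRI finds hypoxia. Section 2.7.2 does not guard against this. The OE MRI calculation method is chosen by test-retest reliability, not by agreement with PET. The BOLD volume is every voxel above the region's own mean plus one SD, which flags about 16% of voxels if values are normal, whether or not the tumour is hypoxic.
- **Power.** Without an SD and an assumed gain, and without saying whether 15% is the effect or the null boundary, the reader cannot tell what the 99% refers to.

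**Working it through.** **A. Comparator.** For each patient,

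predicted painted TCP − observed outcome = (painted TCP − conventional TCP) + (conventional TCP − observed outcome).

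The first bracket is what sections 2.2 and the success rule describe. The second is the calibration error of the model. If painting did nothing but the model overstated control under conventional treatment by more than 15 points on average, the opening wording of 2.3.3 would still show a gain above 15 points.

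**B. Scoring map.** From the article: dose painted by MRI, upward from 60 Gy, threshold 15%. Everything else is assumed for illustration:

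- α 0.15 or 0.3 per Gy; α/β 10 Gy; 30 fractions
- hypoxic fraction 10% or 30%; conventional TCP 5%, 20% or 50%
- escalation limit in the model 66, 72 or 80 Gy, or none (modelling devices only, not dose suggestions)
- 40 simulated tumours of 4,000 voxels per scenario; 2 × 2 × 3 × 4 = 48 scenarios

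Formulas:

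- resistance at oxygen pressure p: g(p) = 3(2.5 + p)/(2.5 + 3p), and f = g(p)/g(40), not below 1
- survival: S = exp{−(αD/f)(1 + d/(10f))}, with d = D/30
- painted dose D = 60·f(MRI), up to the limit; conventional D = 60
- TCP = exp(−N·mean S), with N set so that the conventional plan has the chosen TCP on the true map

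The MRI map is generated independently of the true map (ρ = 0). The same painted plan is scored twice:

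| | Scored on the MRI map | Scored on the independent true map |
|---|---|---|
| Mean gain, range (points) | +11.0 to +94.1 | +0.9 to +11.1 |
| Scenarios with mean gain > 15 points | 46 of 48 | 0 of 48 |

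The two own-map exceptions are +11.0 and +14.9, both at the 66 Gy limit.

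Next, MRI accuracy is varied (α 0.3, hypoxic fraction 20%, conventional TCP 20%, limit 80 Gy):

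| ρ between MRI and truth | 0 | 0.3 | 0.7 | 0.9 | 1 |
|---|---|---|---|---|---|
| Gain on MRI map | 76.8 | 75.8 | 76.6 | 76.1 | 76.3 |
| Gain on true map | 6.3 | 20.4 | 58.5 | 75.1 | 76.3 |

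The own-map gain does not respond to accuracy; the independent-map gain does.

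The meaning of 15% also matters. Because dose only goes up, a random map still gains a little on the true map. At a 5% baseline, +0.9 points is 0.9/5 = 18% relative, which would pass a relative reading.

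**C. Power.** The 99% cannot be reproduced, because its inputs are absent. As a check on the software route, the primary calculation does reproduce: r = 0.7, N = 19, two-sided 5%, point-biserial model (noncentral t, noncentrality √N·r/√(1 − r²)) gives 98.03%.

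For this objective, a one-sided 5% paired t test with N = 20 has 99% power at a standardised effect of 0.922 (noncentrality 0.922 × √20 = 4.12).

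- If 15 points is the effect and the null is zero, the SD may be at most 15/0.922 = 16.3 points. SD 10 gives over 99.9%, SD 20 gives 94.4%, SD 25 gives 82.7% and SD 30 gives 69.5%.
- If 15 points is the null boundary, as the success rule reads, power at a true gain of exactly 15 is 5% by construction. Then 99% needs a true gain of 15 + 0.922·SD: 24.2 points at SD 10, and 29.9 at SD 16.2.

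**The case against.** The strongest reply is that the article never says MRI scores the TCP. It names MRI only for the prescription, and TCP model inputs are detail that a condensed article may leave to the full protocol. A reader might infer that success is guaranteed for any MRI map; the text does not support that. What stands is narrower: the article fixes the painting map, the threshold and the success rule, and that rule as fixed does not require an independent scoring map.

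Second, whether MRI locates hypoxia is tested under the primary objective (Dice above 0.75, correlation above 0.7), so a planning estimate conditional on the map is a fair division of labour. That is reasonable, but success here is not made conditional on the primary result.

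Third, the reference to actual outcomes may be loose wording, since the hypothesis and success rule already compare plans. No stated criterion subtracts observed outcomes from TCP. The contradiction is therefore one to reconcile, not proof that the wrong comparison would be run.

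Fourth, a reader might infer that 99% power for a gain above 15% is impossible. It is not: it holds at a large enough true gain or a small enough SD. The figure is unverifiable, not wrong.

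Finally, the simulated gains depend on assumed radiobiology, and success also needs organ-at-risk metrics to stay similar, which the simulation does not test. Both limits stand. The organ-at-risk condition, however, concerns toxicity and does not check whether MRI is right.

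**Conclusion.** The concern holds in this form. The comparator is contradictory within section 2.3.3 and against section 2.2; this rests on the text alone. The >15% rule can be met by an MRI map that does not locate hypoxia if that map also scores TCP. Under the assumptions above this happened in 46 of 48 scenarios, against 0 of 48 when the same plans were scored on an independent map with 15% read as absolute points. The direction follows from the construction; the sizes are illustrative and leave out the organ-at-risk condition. The 99% power can be neither confirmed nor refuted.

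Severity is should-fix. The objective is secondary and in silico, patients receive standard care, and the primary analysis is untouched. It is nonetheless not among the objectives labelled exploratory in section 2.1, and it carries its own success rule and power claim.

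**What to change.** 1. Define the comparison as modelled TCP of the painted plan minus modelled TCP of the conventional plan, paired within patient. Use observed outcomes only to check the calibration of the TCP model, and reword the opening sentence of 2.3.3 to match.
2. For the success criterion, score both plans on the pre-chemoradiation [18F]MISO map. Section 2.7.4 already co-registers the PET to MRI, resamples it to the finest MRI grid and derives oxygen pressure from it. Report MRI-scored TCP as a secondary, optimistic figure.
3. State whether 15% is absolute or relative.
4. Restate the power with its null, assumed gain and SD.

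The cost is extra computation on scans already scheduled, plus wording. The TCP gain will probably be smaller. Two limits should be acknowledged: PET noise and registration error may lower the gain even for a good MRI map, and the PET and OE MRI volumes share the tumour region and the perfusion condition, so they are not wholly independent. PET scoring also does not make 15 points a demanding bar: in the scan above, a map with ρ = 0.3 still gained 20.4 points. It makes the gain depend on accuracy, and the primary objective's agreement results should be reported beside it.

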**Figure 4 f4:**
[figure not shown]
Example of quantitative images obtained from MRI protocol acquisition on a healthy volunteer.

A region of interest (ROI) will be delineated with a semi-automated tool and checked by an experienced neuroradiologist on the T_2_-weighted image as the hyperintense regions around the tumour. The ROI will be propagated to the T_1_, T_2_, T_2_
^*^ and CBF maps. Voxel-wise and median values of R_1_, R_2_, R_2_
^*^ and CBF within the ROI will be calculated from the quantitative T_1_, T_2_, T_2_
^*^ and CBF maps, respectively. The reproducibility, repeatability and accuracy of the quantitative-MRI protocol will also be assessed using guidelines and a phantom developed by the National Institute of Standards and Technology and the International Society of Magnetic Resonance in Medicine (42).

On one hand, HTV will be defined via OE MRI as the proportion of voxels within the ROI being refractory in R_1_ for O_2_ challenge [i.e. ▵R_1_ ≤ 0, where ▵R_1_ = R_1_ (O_2_) – R_1_ (air)] and well-perfused (i.e. CBF > 0), as previously determined by experts in the field (36, 41, 43, 44). ▵R_1_ will be calculated in two ways. First, it will be calculated from the R_1_ maps obtained from the T_1_-mapping sequences acquired before [R_1_ (air)] and during O_2_ breathing [R_1_ (O_2_)]. Second, it will be calculated from T_1_ maps derived from the T_1_-weighted dynamic acquisition, such that R_1_ (air) is derived from the average of the first two R_1_ maps acquired at baseline while breathing air and R_1_ (O_2_) is derived from the last four R_1_ map acquired during oxygen breathing. ▵R_1_ values obtained with the two approaches will be compared. The approach which will provide the most reliable ▵R_1_ values in the test-retest scan across the entire patient cohort will then be selected to calculate the HTV. Voxel-wise ΔR_1_ values in the HTV will be converted into values of partial pressure of oxygen (pO_2_) using a similar approach to the one used by Chakhoyan et al. (35), which exploits known values of pO_2_ in normal appearing white and gray matter and uses these values to calibrate the pO_2_ values in the tumour. This approach will provide a way to quantitatively measure voxel-wise levels of hypoxia.

On the other hand, HTV will be defined via BOLD MRI by using a previously established method to estimate relative oxygen extraction fraction (rOEF) in human gliomas from T_2_, T_2_

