^*^ and CBV maps (37). Briefly, the transverse relaxation due to local magnetic field inhomogeneities in a blood vessel network, 
$R_{2}^{'}$
, will be calculated within the ROI from T_2_ and T_2_
^*^ maps according to Equation 1:

(1)
$$R_{2}^{'}=R_{2}^{*}-R_{2}=\left(\frac{1}{T_{2}^{*}}-\frac{1}{T_{2}}\right)$$

Then, the Yablonskiy and Haacke model will be applied to derive the oxygen extraction fraction (OEF) according to Equation 2:

(2)
$$OEF=\frac{R_{2}^{'}}{\zeta \cdot \gamma \cdot \frac{4}{3}\cdot \pi \cdot \Delta \chi \cdot B_{0}}$$

where 
ζ
 is the venous fraction of the blood network and approximately equals the venous blood volume (~0.75.CBV), 
$B_{0}$
 is the magnetic field strength, 
γ
 is the gyromagnetic ratio of value 2.675 . 10^8^ s^-1^ T^-1^, 
△χ
 is the susceptibility difference between deoxygenated and oxygenated blood 
$△\chi =△\chi_{0}\cdot Hct=0.924\cdot 10^{-7}$
, which is calculated from the susceptibility difference between fully deoxygenated and fully oxygenated hemoglobin 
$△\chi_{0}=0.264\cdot 10^{-6}$
 and the small-vessel hematocrit (Hct = 0.35). As the absolute quantification of venous CBV in patients is not feasible, the venous blood vessel fraction 
ζ
 is approximated by CBV and the remaining factors are grouped into a constant 
$c=\gamma \cdot \frac{4}{3}\cdot \pi \cdot △\chi \cdot B_{0}=317\;s^{-1}$
. Using these simplifications, rOEF can be calculated according to Equation 3:

(3)
$$rOEF=\frac{R_{2}^{'}}{CBV\cdot c}=\left(\frac{1}{T_{2}^{*}}-\frac{1}{T_{2}}\right)\cdot \frac{1}{CBV\cdot c}$$

To derive the HTV, a hypoxia rOEF threshold (rOEF_hypoxia_) will be defined from the mean, rOEF_mean_, and the standard deviation, rOEF_SD_, of the tissue within the ROI, such that rOEF_hypoxia_ = rOEF_mean_ + rOEF_SD_. Finally, the HTV will be defined by all voxels within the ROI for which rOEF> rOEF_hypoxia_. Hypoxia levels in voxels belonging to the HTV will be measured by rOEF values.

To facilitate the assessment of spatial and quantitative voxel-wise correlations in HTV and in levels of tumour hypoxia defined by the different imaging biomarkers, all MRI images will be resampled into the spatial resolution of the MRI image with the highest resolution by linear interpolation of voxel-wise intensity values.

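### Exploratory secondary objective 3: the Dice > 0.9 label tests near-equal volumes, while the hypothesis is about where the tumour recurs

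*Protocol article*

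**What the plan says.** The hypothesis for secondary objective 3 (section 2.2) is that "MRI measurements of tumour hypoxia at 12 weeks post chemoradiation treatment completion spatially overlap with sites of local recurrence". The outcome measure (section 2.3.4) is "Spatial correlation between HTV after completion of chemoradiation treatment and volume of recurrent tumour at relapse evaluated with standard anatomical imaging", assessed with the Dice coefficient, and "Dice similarity coefficients > 0.9 will be considered a strong spatial correlation". No other criterion is given for the spatial half of the hypothesis; the other half is a Cox regression on overall survival.

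The HTV is built from voxels of an ROI drawn "on the T_2_-weighted image as the hyperintense regions around the tumour" (section 2.7.2). There are two MRI definitions:

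- **OE:** "HTV will be defined via OE MRI as the proportion of voxels within the ROI being refractory in R_1_ for O_2_ challenge", restricted to perfused voxels.
- **BOLD:** "the HTV will be defined by all voxels within the ROI for which rOEF> rOEF_hypoxia", with the threshold set "such that rOEF_hypoxia_ = rOEF_mean_ + rOEF_SD".

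The Introduction describes the biology in the same terms: "Hypoxia, which is often present in subregions of GBM tumours".

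Elsewhere, Dice > 0.75 is called good for MRI against PET at the same timepoint (section 2.3.1), and Dice > 0.9 is called strong for test-retest of one MRI biomarker (section 2.3.2). Section 2.1 labels objectives 3 and 4 exploratory.

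**The concern.** The hypothesis is about location: is the tissue that is hypoxic at 12 weeks the tissue where tumour comes back? Dice answers a different question, namely whether two volumes coincide in both position and size. Here the two volumes are different objects. One is a hypoxic subset of a T2-defined region at 12 weeks. The other is the whole recurrent lesion on anatomical imaging at relapse. There is no stated reason why their sizes should agree to within about 20%.

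The 0.9 label is the only stated yardstick for the spatial result, so it decides how that result is read. A biomarker whose hypoxic voxels all recur would still miss the strong label whenever the HTV is clearly smaller than the recurrence. A reader could then conclude that hypoxia imaging localises recurrence poorly when the shortfall is only a difference in size.

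**Working it through.** The article gives no derivation for 0.9, so there is no figure of the plan to reproduce. The check asks what Dice > 0.9 implies.

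**Inputs.** Cut-off 0.9 (section 2.3.4). BOLD threshold at ROI mean + 1 SD (section 2.7.2). OE HTV: voxels with a change in R1 of zero or less and CBF above zero, with no upper limit on their share of the ROI (section 2.7.2). Recurrence volume: not given, so the ratio h = |HTV|/|R| is an assumption and is varied.

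**Step 1: ceiling on Dice.** Dice = 2|HTV∩R| / (|HTV| + |R|). For given volumes it is largest when the smaller lies wholly inside the larger. If every hypoxic voxel recurs, |HTV∩R| = |HTV|, so Dice = 2h/(1+h).

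**Step 2: ratio needed.** 2h/(1+h) > 0.9 gives h > 0.9/1.1 = 0.818. If instead the recurrence lies inside the HTV, the limit is h < 1.1/0.9 = 1.222.

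**Step 3: ceilings for assumed h, with 100% of the HTV inside the recurrence.**

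| h (assumed) | Maximum Dice |
|---|---|
| 0.10 | 0.18 |
| 0.16 | 0.28 |
| 0.25 | 0.40 |
| 0.50 | 0.67 |
| 0.70 | 0.82 |
| 0.80 | 0.89 |
| 0.82 | 0.90 (0.901) |
| 0.90 | 0.95 |

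The fraction of HTV inside the recurrence is 1.0 in every row.

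**Step 4: a volume from the article.** The Discussion cites a median PET-defined hypoxic volume of 12.85 cm³ in newly diagnosed patients. At that HTV, the recurrence would have to measure between 12.85 × 0.818 = 10.5 cm³ and 12.85 × 1.222 = 15.7 cm³. This is only an illustration, because those patients were not scanned 12 weeks after treatment.

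**Step 5: BOLD.** By the one-sided Chebyshev (Cantelli) inequality, the share of voxels above mean + 1 SD is at most 1/(1+1²) = 0.5 for any distribution. Under normality it is 0.159.

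- If the recurrence is at least as large as the 12-week ROI, then h ≤ 0.5 and Dice ≤ 2(0.5)/1.5 = 0.67 (0.27 with the normal share). Dice of 0.9 is then impossible.
- If the recurrence is smaller than the ROI, 0.9 is possible within a window. With HTV at 50% of the ROI, the recurrence must be 0.5 × 0.818 = 41% to 0.5 × 1.222 = 61% of the ROI. With HTV at 15.9%, it must be 13% to 19%.

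**Step 6: OE.** The definition sets no cap, so 0.9 can be reached, but only inside the ratio window of step 2.

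**The case against.** A reader might infer that 0.9 is unreachable, that the plan requires it, or that the hypothesis therefore cannot be confirmed. The document supports none of these.

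- **Unreachable.** No recurrence volume is given. The HTV is a fraction of its own 12-week ROI, not of the later recurrence. The OE definition has no cap. Impossibility is shown only for BOLD with a recurrence at least as large as that ROI.
- **Required.** Section 2.3.4 attaches a descriptive label. Where the authors set a success rule they say so, as for objective 2 in section 2.3.3. A Dice of 0.4 or 0.67 is still overlap and is nowhere defined as failure.
- **Harsher than the primary objective.** The 0.75 there is labelled good and the 0.9 here strong, so the grades differ. The fair comparison is with section 2.3.2, which gives the same 0.9 label to two scans of the same biomarker. Those should agree far more closely than a hypoxia map and a later anatomical lesion.

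Objective 3 is also exploratory, the sample size does not rest on it, and the Cox analysis is untouched. Finally, containment is not a complete answer: an HTV that lies inside the recurrence but fills 16% of it misses 84%. Dice penalises that miss and containment does not.

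All of this stands, and it limits the strength of the point and shapes the remedy. It does not justify 0.9 for this comparison, for which the article gives no reason.

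**Conclusion.** The point holds in a limited form. The Dice > 0.9 label is mismatched to the hypothesis of section 2.2. It can be earned only if the HTV and recurrence volumes lie within a ratio of about 0.82 to 1.22, however well hypoxia marks the sites of recurrence. That result is exact. How far below 0.9 a well-localising biomarker would fall depends on h, which the article does not give; the ceilings of 0.67, 0.40 and 0.28 are for assumed ratios of 0.5, 0.25 and 0.16. The BOLD result (Dice at most 0.67) needs no distributional assumption but does need a recurrence at least as large as the 12-week ROI. The consequence is a possible misreading of an exploratory result; no primary or powered conclusion is affected. It is worth changing because this label is the only stated criterion for the spatial half of the hypothesis and the change is cheap.

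**What to change.** In section 2.3.4, drop the 0.9 cut-off for this objective and report Dice descriptively. For each MRI biomarker, report:

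1. **Containment (the spatial measure):** the fraction of the 12-week HTV lying inside the recurrence, compared within patient with the fraction of non-hypoxic voxels of the 12-week ROI that recur, as a paired difference with a confidence interval. The paired comparator stops a small HTV or a large recurrence from looking good by default.
2. **Coverage:** the fraction of the whole recurrence covered by the 12-week HTV, counting recurrence outside the 12-week ROI, which the paired comparison cannot see.

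The cost is analysis wording; the scans and segmentations are those already needed for Dice. The downside is that containment alone ignores missed recurrence, which is why coverage and descriptive Dice go beside it. The Discussion accepts that only a subset of patients may contribute to this objective, so the interval may be wide and the number contributing should be reported with it.
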